**The objectives for this proposal are:**

1. To establish age- and sex- appropriate spirometric reference values using the large CLSA population-based spirometric database that is representative in numbers for the age groups of 45- 85 years and the current demographics of the Canadian population.

2. To derive appropriate thresholds for spirometric impairment and severity that relates to co-morbidity, and physical impairment.

3. To examine the prevalence of spirometry impairment and the phenotypes (obstructive versus non-obstructive) and how the phenotype relates to morbidity.

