**Study design, methodology, and data analysis proposed:** Data from the 30,000 participants with spirometry measurements will be included in this proposal. Listed below are the steps that will be undertaken for validation of data quality and statistical analysis. (1) Validation of spirometry quality: As recommended by international guidelines, the quality of the spirometry needs to be individually verified by inspecting the spirographs generated following each effort [9]. If available, these will be inspected to ensure they meet the quality criteria for acceptability and reproducibility by international guidelines. For the higher grade measurements (as assessed by the spirometer software, grades A-C), 30% will be randomly selected for manual inspection by a trained personnel in spirometry reading. An agreement rate between the assessments by manual inspection and the spirometer of >90% will be considered acceptable. For the lower grades (grades D-F), all measurements will be inspected to select out the acceptable values measured with each effort. If spirographs are not available then plausibility of the data will be determined based on the participants age, sex, height and ethnicity. In this case, only grades A-C measurements will be used. Based on the published literature, it is anticipated that up to 30% of spirometry performed outside pulmonary function laboratory setting are considered suboptimal and excluded [11]. Therefore, we anticipate that the final sample size to be approximately 20,000 participants. Those failing to reach international guidelines standards will be explored to see if the same consequences apply i.e. are the standards excessively stringent. This issue is important to address, since the higher standards/guidelines currently being followed may be a major reason why spirometry is not being widely adopted and implemented in the community. Perhaps less stringent quality criteria may be more appropriate if the outcome for its intended use i.e. assessment of morbidity and mortality is the same. (2) Establishing age-, sex-appropriate reference values: A non-linear multiplicative regression model, which adjusts for height, age, sex and ethnicity that we have derived and validated in another large population-based study, PURE [12], will be used to generate reference equations for the CLSA population. These equations will provide the predicted/expected values for the FEV1, FVC and FEV1/FVC according to the height, age, sex and ethnic distribution in the CLSA cohort. The measured FEV1, FVC and FEV1/FVC for each participant will be compared to their predicted values and expressed as a percentage of the predicted (i.e. %pred = measured/predicted x 100). These %pred values provide an indication of the impairment level relative to the overall adjusted population average. A Z-score will then be calculated for each %pred value. The characteristics of participants with a Z-score of 0 or higher (i.e. population mean and higher) will be examined to determine the appropriate selection criteria that enables the selection of participants with the highest adjusted spirometric values in the population. The %pred values generated with this method will then be compared to the traditional selection criteria (i.e. based on self-reported never-smoking and no comorbidities). The relationship between the %pred derived from each method (population-average reference vs healthy cohort-reference), to symptoms, physical impairment and healthcare utilization will be examine to provide face validity to each method. (3) Establishing clinically-meaningful thresholds for diagnosing respiratory impairment that relates to symptoms, physical impairment and health care utilization. Hierarchical logistic regression will be used to establish the adjusted odds ratios (ORs) for symptoms (COPD and heart questionnaires), exercise tolerance (physical activity, 4 minute walk test), functional impairment (IAL, ADL, functional status), health resource utilization (receiving formal and informal care, hospitalization, medication use), across the Z score categories of the ‘population-average reference’. This will provide the magnitude of the relative risks of morbidity associated with each level of lung function impairment (%predFEV1, %predFVC) below the population average; and the relationship across the ORs across different severity of lung function impairment (i.e. linear trend in ORs or other pattern). By examining the relationship between the ORs for morbidity by lung function level will help determine the appropriate threshold to define impairment (4) Defining the different spirometric phenotypes and their relationship to co-morbidities. Spirometric impairment phenotypes will be examined using the threshold established from objective 3 above together with the FEV1/FVC ratio threshold for obstructive (i.e. FEV1/FVC <0.7) vs non-obstructive (>=0.70) phenotypes. Hierarchical logistic regression will be used to examine for any relationship between spirometric phenotypes and self-reported diagnoses of cardiovascular, strokes, neurological, auto-immune/ connective tissue diseases, osteoporosis, osteoarthritis, falls, medication use, hospital utilization. This exploratory analysis will provide insight into the relationship between multi-morbidity and clustering of certain co-morbidities to spirometric impairment phenotypes and the possible underlying mechanistic links/pathways.

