**Amendments to the protocol:**

December 2017: Some of the planned outcome variables such as healthcare utilization, medication use and activities of daily living were not available at the time and therefore were omitted from the analyses.

October 2019: Following the recommendations from ATS, which endorsed the use of the Global Lung Function Initiative (GLI) predictive values for the interpretation of FEV1 and FVC, we elected to remove objective 1 which was to establish our own predictive values using the CLSA spirometry data. Instead we used the GLI predictive values to interpret and grade the severity of FEV_1_.

January 2020: we decided to report on the graded relationship between FEV1 categories with outcomes rather than establishing thresholds since the relationship we observed was continuous throughout the range of the FEV1.

November 2021: Unadjusted analyses were conducted as requested by reviewers from PLOS Medicine and analyses on the FVC

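### The step (4) regressions of phenotype on listed diagnoses cannot by themselves support statements about within-person multi-morbidity or diseases occurring together

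*Protocol*

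**What the plan says.** The analysis is step (4) under the protocol heading 'Study design, methodology, and data analysis proposed'. The exposure is the impairment phenotype, split by "FEV1/FVC ratio threshold for obstructive (i.e. FEV1/FVC <0.7) vs non-obstructive (>=0.70) phenotypes". One method is named: "Hierarchical logistic regression will be used to examine for any relationship between spirometric phenotypes and self-reported diagnoses of cardiovascular, strokes, neurological, auto-immune/ connective tissue diseases", and the list of outcomes continues with "osteoporosis, osteoarthritis, falls, medication use, hospital utilization". The levels of the hierarchy are not stated, nor whether each diagnosis has its own model.

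The next sentence says what this analysis is expected to yield: "This exploratory analysis will provide insight into the relationship between multi-morbidity and clustering of certain co-morbidities to spirometric impairment phenotypes".

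The formal objective behind the step is objective 3: "To examine the prevalence of spirometry impairment and the phenotypes (obstructive versus non-obstructive) and how the phenotype relates to morbidity". It names neither multi-morbidity nor clustering.

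The December 2017 amendment removes some outcomes: "Some of the planned outcome variables such as healthcare utilization, medication use and activities of daily living were not available at the time". None of the dated amendments adds a multi-morbidity outcome or a joint analysis of diagnoses.

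**The concern.** Multi-morbidity means several diseases in one person. Clustering, in its usual sense, means diseases occurring together more often than their separate frequencies would give. Both are features of the joint distribution of diseases within a person. A regression of one diagnosis on phenotype describes that diagnosis only, and a set of such regressions leaves the joint distribution open. The protocol nevertheless attributes the insight on multi-morbidity and clustering to these regressions.

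At stake is how the results may be read. The background section presents lung capacity as a possible indicator of general health, and the hypothesis section postulates accelerated aging that also raises chronic-disease risk. Within-person disease burden bears directly on both ideas. If several diagnoses show raised odds ratios in one phenotype, that pattern is compatible with more, equal or less co-occurrence of those diseases in the same people. The planned output would not tell these apart.

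**Working it through.** The protocol gives no prevalence, effect size or other figure on this point, so there is nothing of its own to reproduce. All prevalences, odds ratios and correlations below are assumptions chosen to test the logic.

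**Two diseases, A and B, in two groups.** The groups are labelled unimpaired and impaired; the same reasoning applies to any two phenotypes.

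- Disease A: 10% unimpaired, 20% impaired. OR = (0.20/0.80)/(0.10/0.90) = 2.25.
- Disease B: 15% unimpaired, 25% impaired. OR = (0.25/0.75)/(0.15/0.85) = 1.89.

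With these margins fixed, P(both) may lie anywhere from max(0, pA + pB − 1) to min(pA, pB). That is 0 to 10% in the unimpaired and 0 to 20% in the impaired. Four choices inside those limits:

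| P(both), unimpaired | P(both), impaired | OR for having both | A-B OR, unimpaired | A-B OR, impaired |
|---|---|---|---|---|
| 1.5% | 5% | 3.46 | 1.0 | 1.0 |
| 5% | 5% | 1.00 | 8.0 | 1.0 |
| 1.5% | 15% | 11.6 | 1.0 | 21 |
| 6% | 4% | 0.65 | 13.5 | 0.70 |

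Example, third row: (0.15/0.85)/(0.015/0.985) = 11.6. Its A-B odds ratio in the impaired comes from the cells both 0.15, A only 0.20 − 0.15 = 0.05, B only 0.25 − 0.15 = 0.10, neither 0.70. This gives (0.15 × 0.70)/(0.05 × 0.10) = 21.

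The first row is independence within each group (0.10 × 0.15 and 0.20 × 0.25). In all four rows the single-disease odds ratios are 2.25 and 1.89. The rows are illustrations, not the limits of what is possible.

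The margins do fix the mean number of the two diseases per person: 0.10 + 0.15 = 0.25 against 0.20 + 0.25 = 0.45. They also fix the bounds on P(both).

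**Eight diseases.** Assume 10% each in the unimpaired and an odds ratio of 1.5 each.

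- Prevalence in the impaired: 1.5 × (0.1/0.9) = 0.1667, and 0.1667/1.1667 = 1/7 = 14.3%.
- Mean count: 8/7 = 1.14, whatever the correlation.
- P(3 or more) under independence: 1 − (6/7)^8 − 8(1/7)(6/7)^7 − 28(1/7)²(6/7)^6 = 1 − 0.2914 − 0.3885 − 0.2266 = 0.0936 (0.09355 unrounded), or 9.4%.
- With a common latent normal correlation, by numerical integration: 14.2% at 0.2 and 16.5% at 0.4.

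The single-disease odds ratios and the mean count do not move, while the share with three or more diseases moves from 9.4% to 16.5%.

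**The case against.** The strongest case on the other side has five parts.

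1. *Separate models are an inference.* The text says only that the regression is hierarchical. A model with diagnoses nested in participants would carry within-person dependence, and nothing excludes it. This stands as a limit on certainty. Step (3) uses the same term for odds ratios of symptoms, exercise tolerance and function with no mention of nesting outcomes in persons, so separate models remain the natural reading. If a joint model is meant, the protocol should say so.

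2. *Clustering may mean which diagnoses gather in which phenotype.* The wording allows this, and the planned odds ratios would address it. They would still not address multi-morbidity, which the sentence names separately.

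3. *The margins are informative.* This is right. They fix the mean count and bound co-occurrence. In the eight-disease example the unimpaired share with three or more is 3.8%, 7.7% and 10.2% at correlation 0, 0.2 and 0.4. At each common correlation the impaired share is therefore higher. The order reverses only if correlation differs strongly by group, for example 0.4 in the unimpaired (10.2%) and 0 in the impaired (9.4%). A reader might infer that the regressions say nothing at all about multi-morbidity; that goes too far.

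4. *The step is exploratory and objective 3 is narrower.* This also stands. A reader might infer that step (4) fails its objective, but the planned models can answer how phenotype relates to morbidity. Nor does the protocol state a rule by which a row of raised odds ratios would be reported as clustering.

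5. *Definitions of this kind belong in a statistical analysis plan.* The exact definition of a count may well sit there, and that plan is not at hand. The mismatch is nevertheless in the protocol's own text, which names both the method and the inference drawn from it.

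Two further inferences are not supported. One is that a single stroke would be counted under several headings: the protocol lists strokes separately and gives no coding. The other is that medication and hospital use would still distort the picture: the December 2017 amendment already omits medication use and healthcare utilization.

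**Conclusion.** The point holds in limited form. As described, the step (4) regressions cannot on their own support statements about within-person multi-morbidity or about diseases occurring together, yet the protocol credits them with that insight. The size depends on assumed prevalences. In the two-disease example, unchanged single-disease odds ratios fit an odds ratio for having both diseases anywhere from 0.65 to 11.6 across four scenarios. In the eight-disease example, the share with three or more varies from 9.4% to 16.5%.

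The conclusion rests on reading the method as one regression per diagnosis, and on reading clustering as co-occurrence within persons; the multi-morbidity part does not need the second reading. The consequence is confined to an exploratory statement. The change is worth making because it is cheap and lets the study address a question it raises itself.

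**What to change.** In step (4), add a per-person count of distinct self-reported diseases. Count each event once, and leave out falls and any utilization items that remain after the December 2017 amendment. Model the count by phenotype with an ordinal or negative binomial model, adjusted as in the planned regressions. Report the proportions with two or more and with three or more diseases by phenotype. These proportions matter because the unadjusted mean count is already fixed by the single-disease prevalences.

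If disease-disease clustering is to be claimed, estimate pairwise associations between diseases within each phenotype and compare them between phenotypes, for example by alternating logistic regression with phenotype in the association model. A stacked model with disease-by-phenotype terms is not enough: it tests whether the phenotype odds ratio differs between diseases. A single working correlation or shared variance would not show whether disease-disease association differs by phenotype.

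If no such analysis is wanted, restrict the sentence to associations of phenotype with each diagnosis and with the disease count.

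Cost: a paragraph of text and one or two extra exploratory models on data already listed, with the modelling assumptions they bring.

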**Amendments to the protocol:**

December 2017: Some of the planned outcome variables such as healthcare utilization, medication use and activities of daily living were not available at the time and therefore were omitted from the analyses.

October 2019: Following the recommendations from ATS, which endorsed the use of the Global Lung Function Initiative (GLI) predictive values for the interpretation of FEV1 and FVC, we elected to remove objective 1 which was to establish our own predictive values using the CLSA spirometry data. Instead we used the GLI predictive values to interpret and grade the severity of FEV_1_.

January 2020: we decided to report on the graded relationship between FEV1 categories with outcomes rather than establishing thresholds since the relationship we observed was continuous throughout the range of the FEV1.

November 2021: Unadjusted analyses were conducted as requested by reviewers from PLOS Medicine and analyses on the FVC

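### FEV1 is reported only in categories although the plan calls its relation with outcomes continuous; a continuous FEV1 term should be added beside them

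*Protocol*

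**What the plan says.** Step (3) of the protocol's section on study design, methodology and data analysis sets the outcome model: "Hierarchical logistic regression will be used to establish the adjusted odds ratios (ORs) for symptoms", followed by exercise tolerance, functional impairment and use of health resources. FEV1 and FVC enter as bands, with odds ratios compared "across the Z score categories" of the population-average reference. Shape is to be read from "the relationship across the ORs across different severity of lung function impairment (i.e. linear trend in ORs or other pattern"). Among the outcomes in this logistic model is "exercise tolerance (physical activity, 4 minute walk test").

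Three entries under Amendments to the protocol bear on this:
- December 2017 omits some outcomes as unavailable. It names healthcare utilization, medication use and activities of daily living as examples, but not the walk test or physical activity.
- October 2019 replaces the study's own predicted values with GLI values, used to interpret FEV1 and grade its severity.
- January 2020 gives up the search for a threshold and reports instead on the "graded relationship between FEV1 categories with outcomes rather than establishing thresholds since the relationship we observed was continuous throughout the range" of FEV1.

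None of these places prints band boundaries or outcome cut-offs, and none names FEV1 as a linear or spline term.

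**The concern.** The amendment rests on a statement about shape: risk changes over the whole range of FEV1, with no natural break. The form of exposure that the document fixes is not well suited to showing or testing that statement. A category odds ratio compares the average person in one band with the average person in another. It carries nothing about differences within a band, and its size depends on how far apart the two bands lie.

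Two things are at stake. First, the reported gradient cannot be compared with that of another study, or with another banding of the same data, without knowing the cuts. Second, if the severity grades put most participants in one normal band, the analysis says little about a gradient within normal values, although the amendment's claim covers the whole range.

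A related point concerns outcomes. If the walk test or physical activity is recorded as a quantity, a binary logistic model needs a cut on it that the scientific question does not need.

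**Working it through.** The plan states no figure for this point (no effect size, alpha, power or cut-points), so there is nothing to reproduce. The steps below size the issue under stated assumptions.

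**1. Information kept by bands.** Assume FEV1 z ~ N(-0.3, 1.1) and a weak linear effect. Let p be the share of people in a band and m the mean standardised FEV1 in that band, m = [φ(a) − φ(b)]/p for standardised limits a and b. The share of FEV1 variance kept is the sum of p·m².

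One-unit bands (assumed cuts 0, -1, -2, -3):

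| z band | p | m | p·m² |
|---|---|---|---|
| below -3 | 0.0071 | -2.781 | 0.055 |
| -3 to -2 | 0.0541 | -1.873 | 0.190 |
| -2 to -1 | 0.2012 | -1.019 | 0.209 |
| -1 to 0 | 0.3452 | -0.170 | 0.010 |
| 0 and above | 0.3925 | 0.979 | 0.376 |
| Sum | | | **0.84** |

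Severity grades (assumed cuts -1.645, -2, -2.5, -3, -4):

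| z band | p | m | p·m² |
|---|---|---|---|
| below -4 | 0.0004 | -3.623 | 0.005 |
| -4 to -3 | 0.0067 | -2.733 | 0.050 |
| -3 to -2.5 | 0.0157 | -2.190 | 0.075 |
| -2.5 to -2 | 0.0384 | -1.743 | 0.117 |
| -2 to -1.645 | 0.0496 | -1.372 | 0.093 |
| -1.645 and above | 0.8893 | 0.212 | 0.040 |
| Sum | | | **0.38** |

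The losses are 1 − 0.84 = 16% and 1 − 0.38 = 62%. With z ~ N(0, 1) instead, the shares kept are 78% and 23%. Equal-sized groups would keep 86% (four) or 90% (five). Scaled to the protocol's anticipated 20,000 participants, 84% and 38% correspond to 20,000 × 0.84 = 16,800 and 20,000 × 0.38 = 7,600 for estimating a linear gradient.

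**2. Dependence on the bands compared.** Take one true relation: odds ratio 1.35 per SD lower FEV1, z ~ N(0, 1), intercept -2 on the logit scale. The odds ratio of the lowest band against the reference band, by numerical integration, is:

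| Lowest band vs reference | Odds ratio | Mean difference d (SD) | 1.35^d |
|---|---|---|---|
| < -1.645 vs ≥ -1.645 | 1.87 | 2.17 | 1.92 |
| < -1 vs ≥ 0 | 1.99 | 2.32 | 2.01 |
| < -2 vs ≥ -1 | 2.18 | 2.66 | 2.22 |
| < -2 vs ≥ 0 | 2.56 | 3.17 | 2.59 |
| < -3 vs ≥ 0 | 3.36 | 4.08 | 3.40 |

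The last column nearly matches the second. The spread arises because different groups are compared, not because any estimate is biased. The effect per SD is 1.35 in every row, and a continuous term reports it directly.

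**3. Cutting a quantitative outcome.** For a normal outcome cut at proportion p, the information kept is φ(c)²/[p(1 − p)], where c is the normal quantile of p:
- p = 0.50: 0.3989²/0.25 = 0.64
- p = 0.25: 0.3178²/0.1875 = 0.54
- p = 0.10: 0.1755²/0.09 = 0.34

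This applies only if the walk test or physical activity is recorded as a quantity and then cut.

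**The case against.** The strongest reply is that the amendment contrasts a gradient with a threshold, not categories with a continuous variable. Ordered bands are a fair way to show a gradient, and category odds ratios are averages within bands that do not assert jumps at the boundaries. That stands: the amendment is not self-contradictory. What remains is that no continuous term is named to test or measure the continuity on which it relies.

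It is also fair that every loss figure rests on assumed cuts. One-unit bands are arguably closer to the Z-score categories of step (3), and there the loss is modest. A continuous model may also sit in an analysis plan that is not shown.

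A reader might infer four stronger criticisms, which the document does not support:
- **Cut-points chosen from the data.** Step (3) already planned Z-score categories, and GLI severity grading was adopted in October 2019, before the January 2020 entry. Nothing says the boundaries came from the observed relation.
- **Categories cannot reveal shape.** Several well-spread bands show coarse shape, and step (3) foresees a "linear trend in ORs or other pattern".
- **Sparse extreme bands as a flaw of categories.** Under the assumptions above, about 0.0071 × 20,000 ≈ 140 people lie below z = -3. A spline draws on the same people there, so it does not cure a thin tail.
- **Residual confounding within wide bands.** That problem comes mainly from coarse adjustment for a confounder; FEV1 is the exposure here.

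The outcome point is an inference, since no scoring or cut-off is printed. It does not apply to outcomes that are binary by nature, such as self-reported diagnoses.

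**Conclusion.** The point holds as a worthwhile, inexpensive improvement, not as an error that invalidates the category results. The current text reports FEV1 in bands, judges shape only from the band odds ratios, and names no continuous term, while its stated reason is continuity over the whole range. The loss of FEV1 information could be as small as about 16% or as large as about 62% under z ~ N(-0.3, 1.1), depending on cuts that are not printed. With some 20,000 participants the loss of power may be the lesser matter, although the document states no effect size against which to judge it. The more lasting benefit is a gradient that does not depend on the bands, together with a direct test of the amendment's own claim. The odds ratios from 1.87 to 3.36 should not be read as instability or bias; they are different contrasts from one relation.

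**What to change.** Keep the category display. Beside it, fit the same adjusted hierarchical models with the FEV1 GLI z-score as a continuous term, using a restricted cubic spline with knots at conventional percentiles. Report the effect per 1 z lower and a test of non-linearity, and show the fitted curve. Because the amendment says the relation had already been observed, label this analysis as added afterwards; neither the knots nor the model can be called prespecified.

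Where the walk test or physical activity is recorded as a quantitative measure, also analyse it on that scale with the linear version of the same model, next to the logistic result.

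No new data are needed beyond the FEV1 and GLI values already in use. The cost is analysis code, one extra figure, two effect scales to explain (ratios and mean differences) and the post hoc label.
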